**Figure 1 f1:**
[figure not shown]
Study design and measurement time points.

### Participants and eligibility

2.3

Participants will be included in this study if(1)Considering that minors under the age of 18 do not have a strong sense of rights and interests to participate in the study, and elderly people over 65 have difficulty in using electronic devices, the inclusion criteria for this study is 18-65 years old age; (2)Currently meets DSM-5 diagnostic criteria for insomnia disorder; (3)Insomnia Severity Index(ISI)total score ≥15; (4)Concomitant anxiety and/or depressive symptoms, 14 points ≤ HAMA ≤ 29, 14 points ≤ HAMD-17 ≤ 23; (5) Adequate literacy and understanding to complete the required inspections and assessments for this study;(6)No sedative, antidepressant, anxiolytic, or antipsychotic medication was taken 2 weeks prior to enrolment, or the type and dose of the medication was stable for 4 weeks prior to enrolment. The type and dose of the drug is stable; (7)they volunteered to participate and signed the ICFs after fully understanding all aspects of the trial.

Participants will be excluded from the study if they meet the following criteria.(1)Other sleep disorders that meet DSM-5 diagnostic criteria, such as apnea syndrome, restless legs syndrome, etc.; (2) female who are pregnant, breastfeeding, or planning to become pregnant during the study period; (3) insomnia problems caused by alcohol or substance abuse; (4) severe cognitive problems; (5) patients with a previous or current diagnosis of bipolar and related disorders, obsessive-compulsive and related disorders, schizophrenia spectrum and other psychotic disorders, trauma and stress-related disorders, dissociative disorders, eating disorders, etc.; (6) patients with significant negative suicidal risk and a HAMD-17 item 2 score of ≥2; (7) patients with a history of epilepsy or other serious physical illnesses; (8) those who have been treated with MECT in the last month; (9) those who have received systematic psychological treatment for more than 3 consecutive months but found it to be ineffective; (10) those who are unable to tolerate the study setting; and (11) those who, in the opinion of the investigator, are unsuitable for the other conditions to participate in this study. For example, the researcher felt that the patient could not guarantee full and complete participation in the study, or that the patient would have a life change such as pregnancy plan that would not be suitable for inclusion in the study.

### Randomization

2.4

Randomization will be based on a computer-generated list of random numbers randomly assigned in a 1:2 ratio to the online psychoeducational group (control group) and the online Smart CBT-I plus group (study group). Later, the computer program will use the generated random list to allocate patients, and the research assistant will inform the trained psychotherapist of the results of the randomized group of patients after allocation, and after the therapist’s interviews, allocate them to the corresponding control and intervention group fellows.

### Intervention

2.5

#### Medication

2.5.1

The patient’s original use of sleep aids, antidepressants, antipsychotics, etc. needs to be maintained at the same dose from the screening period and throughout the intervention period. In case of more pronounced insomnia problems, short-term use of zolpidem or zopiclone or dexzopiclone to assist sleep is permitted, but should not be used for more than 3 consecutive days and cumulatively for more than 2 weeks. Newly prescribed benzodiazepines, antidepressants, anxiolytics, antipsychotics, herbal preparations with sedative effects, and central stimulants are not allowed; self-administration of melatonin and melatonin-related products is not allowed.

#### Online psychoeducational control group

2.5.2

The control group will receive one psychoeducation-related popular science article per day.

Psychological education about sleep disorders aims to provide more scientific and reasonable explanations for different types of insomnia, help patients correctly understand the symptoms of insomnia and the use of insomnia-related medications; teach patients how to cope with ambivalent insomnia, how to cultivate good sleep habits and daily routine; the sleep disturbances that may be encountered in different age groups and the measures to cope with them; sleep-related somatic reactions and common life events that cause sleep disorders. The relationship between insomnia and emotional problems such as anxiety and depression; somatic reactions related to sleep and how to cope with sleep disorders caused by common life events.

The researchers will send a psychological education article through wechat every day, and ask participants to reply “learned.”

Receiving relevant psychoeducation can promote symptomatic improvement (30), and at the same time, there is no immediate risk or indication for medical treatment, so the control group setting is ethically acceptable (31).

#### Online Smart CBT-I plus group (intervention group)

2.5.3

##### Technical overview and customization

2.5.3.1

After random assignment, patients in the Smart CBT-I plus group will enter the 35-day intervention. The Smart CBT-I plus will push fixed tasks for patients to complete every day for 35 days, and after completing the fixed tasks every day, patients can go to the homepage to review the relevant content on their own. If there is any doubt about the content of the treatment or if human support is needed, patients can go to the therapist’s mailbox on the homepage to give feedback, and the therapist will reply within 24 hours to answer questions. The intervention content of Smart CBT-I plus includes sleep hygiene education, relaxation training, sleep restriction, stimulus control and sleep cognitive correction. In addition to the insomnia treatment module, modules for depression and anxiety have been added. Smart CBT-I plus is a self-service psychological intervention platform on WeChat applets for patients with insomnia and emotional problems. The goal of this platform is to solve the current problem of limited psychotherapy resources, rather than replace psychotherapy. In order to design the knowledge structure of Smart CBT-I plus as well as to determine the content, four psychiatrists, three professional psychotherapists and three researchers at SMHC read extensively and studied in depth the literature and books related to sleep disorders, CBT-I, anxiety and depression. During the study design and platform development, several meetings were held to discuss the outline, write and revise scripts, create animations, and collaborate with a professional technology company to develop the program. After development, professionals and real patient groups were invited to do user experience and function tests, and user interviews were conducted for further modification and improvement. Eventually, the WeChat applet platform was completed in 1.5 years and is continuously improved and upgraded.

The “Smart CBT-I plus” applet platform is easily accessible on WeChat, China’s most frequently used application. Participants can easily use the platform from anywhere, with greater flexibility and anonymity.

It features CBT-I technology as the core, integrates cognitive behavioral interventions for anxiety and depression, and has human-computer interaction. It can reduce the number of trips that have to be made to the hospital, making it extremely convenient for patients. This saves travelling time and streamlines the treatment process. In addition, the platform’s online application reduces the amount of time spent in contact with clinicians while minimizing costs, which can make intervention treatment accessible to more populations.

By using the applet’s backend management system, researchers will be able to monitor and track all patients. When patients in either group are at risk of self-injury, suicide, or worsening symptoms of depression and/or anxiety, the researchers, in discussion with the study team, will have the option of stopping the study and assisting the patient to seek medical attention for emergency treatment. All of this will be done with informed consent at the start of the study.

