### Trial design

2.1

This will be a single-center, parallel group, randomized controlled trial. A total of 180 patients with insomnia disorder combined with anxiety and/or depressive symptoms will be recruited and randomly assigned in a ratio of 1:2 to the online psychoeducation group (control group) and the Smart CBT-I plus treatment group (study group), and followed up at 6 months, and 12 months after the treatment. Both the control and study groups will be done online.

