##### Integrative support approach

2.5.3.2

After logging into the WeChat app and completing the registration, the patient receives a short welcome message and a brief overview of the intervention’s format, modules, method of operation, and principles of treatment. At the same time, the patient is required to provide the necessary personal information, and after completing the opening, the patient will enter the daily intervention training.

Smart CBT-I plus is primarily based on the core techniques and principles of CBT-I, while incorporating Cognitive Behavioral Therapy (CBT) for anxiety and depressive symptoms. Stimulus Control Therapy, Sleep Restriction Therapy, Cognitive Therapy, Sleep Hygiene Education and Relaxation Training (20, 32), the 5 components were among the most commonly used components of CBT-I (33–35).

Patients with sleep disorders commonly co-morbidly suffer from anxiety and/or depression, which are closely related and interact with each other. Cognitive Behavioral Therapy (CBT) is a common treatment for symptoms of anxiety and depression with proven results (36, 37).

By the development of good sleep habits, the correction of sleep cognition, and the customization and implementation of personalized treatment strategies, sleep-related maladies and cognitions can be effectively reduced, and the development of chronic insomnia can be avoided through correct behavioral modification. The treatment consists of animation, audio, video, quizzes and email support from the therapist, making it a lively and varied program. The daily treatment and learning tasks are pushed to the patient between 3-5 minutes in length. The treatment tasks are linear, starting with a review of the previous day’s content, followed by the presentation of the day’s tasks, the last task of the day is a relaxation exercise, which can be done at any time throughout the day and with the audio of your choosing, followed by a reminder to go to the home page, which reminds you to go to self-help interventions for anxiety and depression, and then finally to the home page, which allows you to review the past treatments and learning content.

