### Participant timeline

2.6

At baseline and at the end of the intervention, patients will be subjected to a series of psychological assessments, including sleep and mood symptoms. For patients in the study group, at the end of the 35-day intervention, a random sample of 30 patients will also be given a one-on-one qualitative interview to discuss their experience with Smart CBT-I plus, the interview results will be recorded. All patients will be evaluated at follow-up at 6 and 12 months after completion of treatment. Patients will be made aware of all assessment results. They will also be able to view their weekly assessments on their own in the program. they will still be able to use the program on their own after the 35-day session. The specific follow-up schedule is shown in **Table 1**.

**Table 1 T1:** Subject visit schedule.

items	Screening visit	Baseline visit	Post-intervention visit	Follow-up visit	
Visit	V0	V1	V2	V3	V4
Time	Day -7-0 * (± 1 day)	Day 0 (± 1 day)	35 days after baseline (± 3 days)	6 months after intervention (± 7 days)	12 months after intervention (± 7 days)
Sign informed consent	**×**				
Inclusion/exclusion criteria	**×**	**×**			
Self-made general demographic questionnaire		**×**			
Self-made clinical feature collection scale		**×**			
Semi-structured sleep assessment questionnaire		**×**			
Insomnia Severity Index Scale (ISI)	**×**	**×**	**×**	**×**	**×**
Hamilton Depression Scale (HAMD)	**×**	**×**	**×**	**×**	**×**
Hamilton Anxiety Scale (HAMA)	**×**	**×**	**×**	**×**	**×**
Clinical Gross Impression Scale (CGI)		**×**	**×**	**×**	**×**
Epworth Sleepiness Scale (ESS)		**×**	**×**	**×**	**×**
Pittsburgh Sleep Quality Index Scale (PSQI)		**×**	**×**	**×**	**×**
Hygiene economics evaluation		**×**	**×**	**×**	**×**
Adverse event report form			**×**	**×**	**×**
Serious Adverse Event (SAE) report form			**×**	**×**	**×**
Six quality of life questionnaires		**×**	**×**	**×**	**×**
Generalized Anxiety Scale (GAD-7)		**×**	**×**	**×**	**×**
Dysfunctional Beliefs and Attitudes about Sleep Scale (DBAS-16)		**×**	**×**	**×**	**×**
Rapid Report of Depressive Symptoms - Self-report score 16 items (QIDS-SR16)		**×**	**×**	**×**	**×**
Life Event Scale (LES)		**×**			
Therapeutic Alliance Questionnaire Revision (WAI-S)			** *×* **		
Outline of semi-structured qualitative interviews (30 patients of study group)			** *×* **		
medication administration record	**×**	**×**	**×**	**×**	**×**

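### The safety stop is promised in both arms, but no scheduled contact with controls before day 35 carries the symptom information to trigger it, and patients stopped before any follow-up drop out of the FAS

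*Protocol article*

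**What the plan says.** **Monitoring and stop.** Protocol article, 2.5.3.1, lies within the description of the Smart CBT-I plus arm. It says that by using the applet's "backend management system, researchers will be able to monitor and track all patients". It continues: "When patients in either group are at risk of self-injury, suicide, or worsening symptoms of depression and/or anxiety", the researchers, after discussion with the study team, "will have the option of stopping the study and assisting the patient to seek medical attention for emergency treatment".

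**Who uses the applet.** Registration is described in 2.5.3.2, again under the study arm: "After logging into the WeChat app and completing the registration, the patient receives a short welcome message". For controls, 2.5.2 says: "The researchers will send a psychological education article through wechat every day, and ask participants to reply" with a single word confirming that the article was studied. Section 2.1 adds "Both the control and study groups will be done online", without saying that the arms share a platform.

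**Schedule.** In Table 1 (2.6), HAMD, HAMA, GAD-7 and QIDS-SR16 are marked at V1 and next at V2. The adverse event form and the "Serious Adverse Event (SAE) report form" are first marked at V2. The text of 2.6 also says: "They will also be able to view their weekly assessments on their own in the program". It names neither arm nor instrument, and Table 1 has no such row.

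**Withdrawal and analysis set.** Section 2.8 lists grounds for withdrawal, including a serious adverse event, prohibited therapies and poor compliance, but not worsening mood or self-harm risk. Section 4 limits the FAS to patients with at least one follow-up and data on the key indicators, makes the FAS the main analysis, and plans multiple imputation for missing data.

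**The concern.** A stop rule protects a patient only if someone can see its trigger. The rule covers both arms, but the mechanism named for it is the back end of a tool that the article describes only as the study arm's treatment. Controls enter with anxiety and/or depressive symptoms (limits HAMA 14–29 and HAMD-17 14–23, section 2.3), and 2.5.1 bars newly prescribed antidepressants and anxiolytics during the intervention. Timely detection of worsening therefore matters for them.

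The second issue is what happens to the data after a stop. The text speaks of stopping the study, not the intervention, and neither 2.5.3.1 nor 2.8 says that V2–V4 are still collected. If a patient is stopped before V2 and not seen again, the FAS rule removes that patient from the main ISI comparison. Such patients are not a random subset, because they are removed for doing badly.

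**Working it through.** No figure in the plan needs to be reproduced here. The check sets the sections side by side.

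1. **Length of the interval.** V1 is day 0. V2 is 35 days after baseline, ± 3 days, so 35 − 3 = 32 to 35 + 3 = 38 days. Table 1 has no visit column between them, in either arm.

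2. **Described contact with controls in that interval** (planned n = 60):
   - daily WeChat article and acknowledgement (2.5.2): a two-way channel, but the requested reply says nothing about symptoms;
   - applet log-in, registration or mailbox: described only under 2.5.3;
   - weekly in-program assessments (2.6): arm and content not stated.

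3. **Described contact with the study arm** (planned n = 120):
   - applet use, therapist mailbox answered within 24 hours, and automatic weekly feedback (2.5.3.1 and 2.5.3.2);
   - the one feedback example concerns sleep latency, sleep time and sleep efficiency. No staff-reviewed mood or self-harm alert is described, so better detection in this arm is plausible but not shown.

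4. **Consistency of 2.5.3.1 with 2.5.2.** Either controls are not in the back end, and the claim to track all patients fails for 60 of 180, one third of the sample; or they are, and 2.5.2 does not say what they register for or what is seen. Either way the text needs a sentence.

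5. **From stop to analysis set.** A patient is stopped (2.5.3.1) or withdrawn (2.8) before V2:
   - if seen later at V3 or V4 with ISI data, the patient may still satisfy the at-least-one-follow-up rule, and the missing V2 ISI could be imputed;
   - if not seen again, the patient is outside the FAS, and imputation applied within the FAS cannot restore the patient.

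6. **Scale.** The plan's allowance for loss is 15% (2.7), or 0.15 × 180 = 27 patients. That is for all reasons. The share stopped or withdrawn before any follow-up is not given, nor is the rate of worsening or how either would differ by arm. A bias in the ISI comparison therefore cannot be computed from the document.

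**The case against.** The strongest reply is that control registration is inferred from silence. No sentence puts controls outside the back end, 2.5.3.1 says all patients, and a condensed article may leave registration and between-visit reporting to the full protocol. This stands. A reader might infer that controls are unmonitored, and the document does not support that.

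Further mitigations also stand. V2 forms can record events from days 0–35 in retrospect. Controls can report trouble over a channel used every day, and a missing reply is visible. Entry excludes significant suicidal risk and caps severity, and a therapist interview of about an hour screens out unsuitable patients. A patient may withdraw at any time, so the ban on new drugs traps nobody. The Table 1 gap is the same in both arms, so its length is no evidence of a defect specific to controls.

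It can also be said that the stop plainly concerns the individual patient, and that 2.8 need not repeat its grounds. That is fair as to meaning, but it leaves open whether outcome data are still collected.

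What the reply does not remove is that the article chose to state its monitoring mechanism, and that mechanism does not match the control arm it describes. Retrospective recording at V2 does not serve an emergency referral. The FAS rule is stated outright and does not depend on how controls are monitored.

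**Conclusion.** The concern holds in a limited form, and the text should be changed. As described, no scheduled contact with controls carries the symptom information needed to trigger the stop before day 35. This is a gap in timely detection as written, not proof that surveillance is absent. It rests on reading 2.5.2 as a full account of control contact, which the full protocol may supplement.

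Separately, the stated FAS rule removes patients who are stopped or withdrawn before any follow-up, so the planned imputation cannot act on them. A reader might go further and infer that unequal detection tilts the primary ISI comparison towards Smart CBT-I plus. The document does not support that. Better detection in the study arm is not shown, worsening controls may also leave or be withdrawn for a prohibited therapy, and no rates are given. Size and direction are both unknown, and if stopping is equal in the two arms the bias may be nil.

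**What to change.** **Monitoring.** State in 2.5.2 how controls are monitored: in the back end or through the daily WeChat contact. During the 35 days, send both arms the same brief check by WeChat: the QIDS-SR16 already in Table 1 plus one direct self-harm question. Record adverse and serious adverse events from day 0. Send flags to the study team, with the threshold set by the clinicians before the first patient enters.

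**Stop and analysis set.** In 2.5.3.1, make the stop a stop of the intervention for that patient, and name this ground in 2.8. With consent, keep collecting ISI at V2–V4. Define the FAS as all randomised patients with a baseline ISI, and use the planned multiple imputation where the V2 ISI is missing. Continued collection matters more than imputation, because baseline data alone say little about a patient who was stopped for worsening.

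**Cost.** If the check is sent twice, for example at days 14 and 28, that is 180 × 2 = 360 short questionnaires (240 study, 120 control) over a channel already in use. No visit is added. Self-harm answers need prompt clinical review; the article gives no staffing figures, so that time must be planned. Controls get slightly more contact, which may slightly reduce the contrast between arms. The wording of 2.5.2, 2.5.3.1, 2.8, section 4, Table 1 and the consent text changes.

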##### Integrative support approach

2.5.3.2

After logging into the WeChat app and completing the registration, the patient receives a short welcome message and a brief overview of the intervention’s format, modules, method of operation, and principles of treatment. At the same time, the patient is required to provide the necessary personal information, and after completing the opening, the patient will enter the daily intervention training.

Smart CBT-I plus is primarily based on the core techniques and principles of CBT-I, while incorporating Cognitive Behavioral Therapy (CBT) for anxiety and depressive symptoms. Stimulus Control Therapy, Sleep Restriction Therapy, Cognitive Therapy, Sleep Hygiene Education and Relaxation Training (20, 32), the 5 components were among the most commonly used components of CBT-I (33–35).

Patients with sleep disorders commonly co-morbidly suffer from anxiety and/or depression, which are closely related and interact with each other. Cognitive Behavioral Therapy (CBT) is a common treatment for symptoms of anxiety and depression with proven results (36, 37).

By the development of good sleep habits, the correction of sleep cognition, and the customization and implementation of personalized treatment strategies, sleep-related maladies and cognitions can be effectively reduced, and the development of chronic insomnia can be avoided through correct behavioral modification. The treatment consists of animation, audio, video, quizzes and email support from the therapist, making it a lively and varied program. The daily treatment and learning tasks are pushed to the patient between 3-5 minutes in length. The treatment tasks are linear, starting with a review of the previous day’s content, followed by the presentation of the day’s tasks, the last task of the day is a relaxation exercise, which can be done at any time throughout the day and with the audio of your choosing, followed by a reminder to go to the home page, which reminds you to go to self-help interventions for anxiety and depression, and then finally to the home page, which allows you to review the past treatments and learning content.

The 5 insomnia treatment modules and 2 emotional intervention modules are as follows: Stimulus control is to enhance the connection between the bed and sleep and weaken the association between the bed and other activities such as eating, reading, etc., and thus making it easier for the patient to fall asleep. Restoring the bed to its function as a sleep-inducing signal. Sleep restriction is the process of improving sleep efficiency by reducing the amount of non-sleep time spent in bed. The main goal of cognitive therapy is to correct irrational cognitions related to sleep. Sleep Hygiene Education helps to establish good sleep habits. Relaxation training is used to regulate the patient’s emotional state. The treatment modules for anxiety and depression provide a wide range of self-help techniques for emotional intervention that are easy to follow and learn. In the anxiety module, it will help to identify the patient’s distorted cognition, conduct truthfulness testing, develop alternative thinking, etc. to correct the patient’s distorted cognition, and finally help the patient to accept themselves through positive self-suggestion. In the depression intervention session, we explained the knowledge about depression through voice and text, and then targeted intervention on depressive symptoms through mood logging, behavioral activation, task grading, and cognitive remediation. Screenshots of the homepage and part of the interface are shown in **Figure 2**.

